## Abstract

**Introduction:**

Flexible sigmoidoscopy (FS) screening is associated with reduced colorectal cancer incidence and mortality when offered as a one-off test to men and women aged 55–64. The test, also referred to as the ‘bowel scope screening’ (BSS) test, was added to England’s national Bowel Cancer Screening Programme in March 2013, where it is offered to men and women aged 55. Since its implementation, uptake of the BSS test has been low, with only 43% of the eligible population attending an appointment. Sending non-participants a reminder at age 56 has been shown to improve uptake by up to nine percentage points at a single centre in London; we hypothesise that adding a general practitioners (GPs) endorsement to the reminder could improve uptake even further.

**Methods and analysis:**

This paper describes the protocol for a randomised controlled trial which will examine the effectiveness of adding a GPs endorsement to a reminder for BSS non-participants aged 56. All screening-eligible adults who have not responded to a BSS appointment at London North West Healthcare NHS Trust within 12 months of their initial invitation will be randomised to receive either a GP-endorsed reminder letter or reminder letter without GP endorsement. The primary outcome will be the proportion of individuals screened within each group 8 weeks after the reminder. Statistical comparisons will be made using univariate and multivariate logistic regression, with ‘uptake’ as the outcome variable, GP reminder group as the exposure and sociodemographic variables as covariates.

**Ethics and dissemination:**

The study was approved by the Yorkshire & Humber—Bradford Leeds Research Ethics Committee (16/YH/0298) and the Confidentiality Advisory Group (17/CAG/0162). The results will be disseminated in a peer-reviewed journal in accordance with the Consort statement and will be made available to the public.

**Trial registration number:**

ISRCTN82867861

Strengths and limitations of the studyIf effective, this study will provide a cost-effective means to promote uptake of flexible sigmoidoscopy (FS) screening in an organised programme.The key importance of this randomised controlled trial protocol is that it highlights a methodology for delivering general practitioner (GP)-endorsed reminders to examine whether a 12 months’ reminder letter can be further enhanced to improve screening uptake in an organised FS-based screening programme for colorectal cancer.There is a strong public health mandate to develop system-friendly interventions to promote uptake of the bowel scope screening programme in England, particularly among socioeconomically deprived groups, where the potential for improving uptake is greatest.The study population is limited to the patients who are registered at the participating GP practices in London Boroughs of Hillingdon, Harrow and Brent.

## Introduction

Colorectal cancer (CRC) is the fourth most common cancer in the UK and the second leading cause of cancer deaths.^1 2^ Screening is able to improve survival by detecting CRC early, when it is more treatable.^3–6^ Screening can additionally prevent cases through the early detection and removal of adenomas: the precancerous lesions from which most CRCs develop.^7–9^

Randomised controlled trials (RCTs) examining the effectiveness of flexible sigmoidoscopy (FS) screening to improve CRC outcomes highlight that disease-specific mortality and incidence are reduced by 32% and 50%, respectively, when the test is performed just once between the ages of 55 and 64.^8 10–12^ On this basis, the National Health Service (NHS) in England added ‘once-only’ FS screening for men and women aged 55 (known as bowel scope screening, BSS) to the National Bowel Cancer Screening Programme (BCSP) in March 2013.^13^ Since that time, uptake of FS in the English BCSP has been only 43%,^14^ which is considerably lower than the uptake for the faecal occult blood test (FOBt) which is offered biennially to those aged 60–74, and dramatically lower than the rates observed for breast and cervical screening (54%, 76%, 78%, respectively,^15–17^).

Barriers to FS screening include practical barriers (ie, inconvenient appointment time, difficulties travelling to the appointment and so on), worry about pain, discomfort or injury associated with the examination, and not wanting to know about any health issues.^18^ Several studies attempting to address these barriers have examined the use of self-referral reminders (reminders which prompt former non-participants to self-refer for screening) 12 and 24 months after their initial invitation.^19–21^ These have been shown to facilitate uptake in as much as 21.5% of former non-participants. While these results are highly promising, the annual reminder concept is still relatively unexplored, and there is considerable scope for modification and refinement of the intervention content. For example, there is now considerable evidence that a general practitioner (GP) endorsement of cancer screening is positively associated with uptake.^22–24^ Previous research examining the relative importance of barriers to CRC screening indicate that primary care should play a key role in encouraging uptake, highlighting that the two most important barriers to CRC screening among individuals who have never been screened are ‘failure of the clinician to suggest screening’ and ‘not knowing testing was necessary’.^25^

A recent study conducted in Australia demonstrated that a theory-based modification to the advanced notification letter improved uptake among men and was highly cost-effective.^22^ A recent review has found that the inclusion of a GP’s endorsement on the invitation letter can improve uptake of CRC screening with the FOBt; however, none of the studies identified in the review used FS screening uptake as an outcome.^26^ This paper describes the protocol for an RCT which will examine the effectiveness of adding a GP endorsement to a reminder sent to BSS non-responders 12 months after their initial invitation.

## Aims

The primary aim of this RCT will be to test whether adding a GP endorsement to the 12 months’ reminder letter improves the uptake of BSS among previous non-responders over and above a 12-month reminder letter without a GP endorsement. The secondary aim will be to examine demographic differences in uptake in response to the GP-endorsed reminder letter and the standard annual reminder letter (ie, a reminder without a GP endorsement).

## Methods and analysis

### Study design

This study will be a non-clinical RCT with two parallel arms (see figure 1). The intervention group will receive a GP-endorsed reminder letter (online supplementary appendix A) by post, the control group will receive the same reminder letter by post, minus the GP endorsement (online supplementary appendix B).

10.1136/bmjopen-2018-022263.supp1Supplementary data

10.1136/bmjopen-2018-022263.supp2Supplementary data

**Figure 1 F1:**
[figure not shown]
GP-endorsed reminders Consort flow diagram. GP, general practitioner; NHS, National Health Service.

### Study setting

This RCT will be conducted in London, England, at London North West Healthcare NHS Trust in Harrowin Summer 2018.

### Eligibility criteria

Adults will be eligible to take part in the study if they: (1) are aged 56 years at the time of enrolment, (2) are registered with a consenting general practice served by the BSS centre at London North West Healthcare NHS Trust, (3) have been offered but not responded to a routine BSS appointment for at least 12 months, (4) meet the clinical eligibility criteria for BSS and (5) have not opted out from sharing their personal data for purposes beyond direct care (from here on referred to as type 2 objectors).

NHS Digital, formerly known as the Health and Social Care Information Centre, will be responsible for identifying potentially eligible adults and excluding any individuals who do not meet the criteria for the study. NHS Digital will exclude individuals if they: (1) have an open episode status, for example, postponed the appointment to another date; (2) contacted the screening centre and declined; (3) contacted the screening programme and were deemed medically unfit; (4) contacted the screening programme to confirm they would be attending their appointment, but then did not attend.

### Blinding and randomisation

Adults who are eligible for inclusion will be entered into a computerised study database and randomised (in a 1:1 ratio) to receive either a ‘standard reminder letter’ or a ‘GP-endorsed reminder letter’ 12 months after their initial invitation using simple pseudorandom allocation methods.

### Preintervention phase: recruitment of practices

We will send invitations to GP practices which are being served by London North West Healthcare NHS Trust and have been included in the BSS programme for at least 12 months. Consenting GP practices will be permitting their practice name to be included in the GP-endorsed reminder letter. Using a recruitment strategy similar to a recent RCT with GP practices in London, we are expecting approximately 50% of GP practices to sign up using a strategy of email invitations and weekly reminders.^27^

### Intervention phase: reminder delivery

#### The 12 months’ reminder letter (standard reminder group)

The standard reminder letter will be the same reminder letter that was used in the previous trials (see online supplementary appendix A
19–21). It will be a personally addressed letter from BSS centre at the North West London Hospitals Trust that will invite recipients to make an appointment by returning an ‘appointment-request slip’ or calling the Freephone number at the screening centre. As with the previous trials, the reminder will also give recipients the option to express a preference for the day and time of their appointment.

#### The 12 months’ reminder letter with GP endorsement (intervention group)

The GP-endorsed reminder letter will be the same as the standard reminder letter, except that it will contain an additional statement of GP endorsement which states: ‘Your GP practice, xxxx xxxxx, supports the NHS Bowel Scope Screening Programme’ (see online supplementary appendix B).

### Timeline

Twelve months after receiving an initial invitation for BSS, all eligible adults will receive a reminder letter (either the endorsed or standard letter) with the option of indicating preferred days and times to schedule their BSS appointment at the screening centre based at London North West Healthcare NHS Trust.

### Sample size calculation

The study has been designed to detect a five percentage point increase in uptake between the GP-endorsed and standard reminder group. As a GP-endorsed reminder has not previously been tested in the context of an organised FS screening programme for CRC, the estimates for this study were based on the effect size of using GP endorsement to promote uptake of screening for CRC using alternative tests (such as the FOBt^22–24^). Hewitson and colleagues^24^ found that the response rate of individuals receiving usual care, versus a GP-endorsed invitation letter, increased the rate of response by 5%, from 10% (as observed for a standard reminder in previous work) to 15%. To detect this increase in uptake with 80% power at the 5% alpha level, with two-sided testing, approximately 600 participants per trial arm are required, giving a total sample size of 1200 participants.

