### Data processing and data collection

Identification: Adults will be identified by NHS Digital only if they are registered with a consenting GP practice. Identification of eligible participants will take place using data contained within the Bowel Cancer Screening System which provides an up-to-date electronic record of uptake data for individuals enrolled in the national BSS.Data cleanse: NHS Digital will query the data of non-participants to identify type 2 opt-outs. Using the cleansed dataset, the first 1200 individuals will be selected to be included in the RCT database.Randomisation: NHS Digital will randomise eligible participants using the prerandomised dataset. The database will be split into two separate files with an equal number of people in each document using the study groups.Intervention: NHS Digital will share the data associated with each mail-out for the intervention and the control group with the mailing company called CFH Docmail Limited. CFH Docmail is an NHS Information Governance toolkit accredited mailing company that will be facilitating the mail merge throughout the study. The dataset will include study group, unique ID, personal contact details, NHS number and the practice name (only for intervention group). Reminders will be produced by merging each study group database with the reminder letter templates. The full package will include: the reminder letter, standard information booklet and a freepost return envelope. This process of sending previous non-participants a reminder 12 months after their initial invitation will continue until the study sample size (n=1200) is reached. We plan to send out 150 letters per week and send out all the reminders in 8 weeks.Data generation: once letters are sent, we will allow 8 weeks for all individuals to respond to the self-referral reminder. At the 16th week of the trial, NHS Digital will query the screening episode status of all individuals using their NHS numbers. If previous non-responders did not respond, their status will not change, and they will remain ‘non-responders’. If people confirmed and attended their appointment, they will be coded as ‘attended’. If people contacted the centre and cancelled their appointment and did not book another appointment, they will be considered ‘decliners’. If someone confirmed an appointment but did not attend, they will be coded as ‘non-attenders’. We will also request a separate category for those who have contacted the screening centre, had the initial confirmation and attended the clinic but not eligible to have the full investigation. People will be adequately screened, if they have had the full bowel scope investigation and received a definitive clinical result. For this purpose, we will additionally request the screening outcome of those who had the screening, and also information about the follow-up colonoscopy investigations. As a result, we will be able to distinguish between: (1) those who reacted to the self-referral reminders (responders) versus those who did not (non-responders), (2) those who successfully attended screening (attenders) versus those who did not (non-attenders) and (3) those who were adequately screened versus those who were not. In addition, NHS Digital will provide the Index of Multiple Deprivation (IMD) scores, using the postcodes of each individual included in the study.Data extraction: At the end of the study, after all data have been collated, the study database will be duplicated by NHS Digital. One copy will be anonymised for analysis by the University College London (UCL) research team. In the anonymisation process, all identifiable information including NHS number, full name, address, GP code and GP name will be excluded.Data deletion: Once the anonymised dataset is sent to the research team at UCL and verified, the research team will ask CFH Docmail to destroy all the datasets that were shared by NHS Digital. Only the research team at UCL will have access to the final dataset.

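### 600 per arm gives about 75% power, not the stated 80%, for 10% versus 15% at two-sided 5%

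*Protocol article*

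**What the plan says.** The protocol article, under *Sample size calculation*, describes the trial as "designed to detect a five percentage point increase in uptake between the GP-endorsed and standard reminder group". Uptake is assumed to rise "from 10% (as observed for a standard reminder in previous work) to 15" per cent. The error rates are set by "with 80% power at the 5% alpha level", and the result is given as "with two-sided testing, approximately 600 participants per trial arm are required, giving a total sample size of 1200 participants". *Blinding and randomisation* specifies equal allocation.

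*Data processing and data collection* then treats 1200 as a fixed operational target. The first 1200 people in the cleansed dataset are selected, and mailing "will continue until the study sample size (n=1200) is reached". The article states no allowance for dropout, clustering or an interim look. *Statistical analysis* plans individual-level logistic regression, both unadjusted and adjusted for gender and the deprivation index.

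**The concern.** The rates, power, alpha, sidedness and allocation ratio are all printed, so the sample size can be recomputed without assumptions. For 10% versus 15% with two-sided 5% alpha and 80% power, a figure near 685 per arm is expected, and 600 is visibly short of it.

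This is the trial's only power statement, and it supports the primary aim. If the result is null, readers will use it to judge whether a 5-point benefit of the endorsement can be set aside. Because recruitment stops at 1200, no over-recruitment can be expected to restore the stated power.

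**Working it through.** **Inputs** (from *Sample size calculation*, with allocation from *Blinding and randomisation*): p1 = 0.10, p2 = 0.15, difference 0.05, mean rate 0.125; two-sided alpha 0.05 (z = 1.960); power 0.80 (z = 0.8416); allocation 1:1; stated n = 600 per arm.

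**1. Required size, pooled variance under the null**

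n = [1.960 × √(2 × 0.125 × 0.875) + 0.8416 × √(0.10 × 0.90 + 0.15 × 0.85)]² / 0.05²

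- First term: 1.960 × 0.4677 = 0.9167
- Second term: 0.8416 × √0.2175 = 0.8416 × 0.4664 = 0.3925
- n = (1.3092)² / 0.0025 = 685.6, so 686 per arm (1372 in total)

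The stated 600 is not reproduced.

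**2. Other methods**

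| Method | n per arm |
|---|---|
| Two-sided, pooled | 686 |
| Two-sided, unpooled: (1.960 + 0.8416)² × 0.2175 / 0.0025 = 682.9 | 683 |
| Two-sided, arcsine | 681 |
| Two-sided, Wald test of the log odds ratio | 696 |
| Two-sided, continuity-corrected | 726 |
| One-sided, pooled | 540 |
| One-sided, continuity-corrected | 580 |

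No two-sided method gives 600. The one-sided figures do not give it either, and they would contradict the stated test.

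**3. Power at 600 per arm**

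z = (0.05 × √600 − 0.9167) / 0.4664 = (1.2247 − 0.9167) / 0.4664 = 0.6605, so power = Φ(0.6605) = 74.6%.

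| Two-sided method | Power at 600 per arm |
|---|---|
| Pooled normal approximation | 74.6% |
| Unpooled normal approximation | 74.7% |
| Arcsine | 74.9% |
| Wald log odds ratio | 74.0% |
| Exact enumeration, uncorrected chi-square | 74.8% |
| Exact enumeration, continuity-corrected chi-square | 72.1% |

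As a check, the pooled approximation at 686 per arm returns 80.0%.

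**4. What 600 per arm can detect**

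Holding p1 = 0.10 and solving the pooled formula for 80% power at n = 600 gives p2 = 0.1538, a difference of about 5.4 points.

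**5. Shortfall**

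686 − 600 = 86 per arm (86/686 = 12.5%); 683 − 600 = 83 per arm (83/683 = 12.2%). In total this is 166 to 172 participants.

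**The case against.** The arithmetic is not in dispute; the case on the other side is about how much it matters.

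- **The figure is given as approximate and the gap is modest.** Required size is sensitive to the planning rates, and 600 per arm does give 80% power for 5.4 points instead of 5.0. That is a fair account of the scale. However, rounding 683 or 686 gives 680, 690 or 700; it does not give a number 12% to 13% lower.
- **The 10% may be a rounded control rate.** As an assumption only, 8.5% to 13.5% needs 614 per arm, 8% to 13% needs 589, and 9% to 14% still needs 638. A control rate of about 8% to 8.5% would therefore bring the answer close to 600. Nothing in the article says such a rate was used, and the printed rates are 10% and 15%, so this does not rescue the statement as written.
- **Covariate adjustment could change the power.** These figures are for the unadjusted comparison. The article gives nothing from which to quantify the effect of adjusting for gender and deprivation, and it claims no gain from it. The restated power should be labelled as unadjusted; that part of the objection stands.
- **Validity is untouched.** This is correct. Randomisation, outcome, estimate, confidence interval and type I error do not depend on the power statement.

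**Conclusion.** The concern holds. On the article's own inputs, 600 per arm gives about 75% power (74.0% to 74.9% across uncorrected two-sided methods, 72.1% with continuity correction). The type II error is about 25% instead of 20%, a relative increase of one quarter. Reaching 80% needs 83 to 86 more per arm, or about 126 more with continuity correction (726 − 600).

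The conclusion rests on the printed rates, equal allocation, an unadjusted individual-level comparison and complete outcome data on all 1200. The error is confined to a planning claim, but as written that claim describes a property the design does not have, so it must be corrected.

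**What to change.** Keep 1200 participants and replace the concluding sentence of *Sample size calculation* with wording such as: *600 participants per arm give about 75% power (unadjusted comparison, two-sided 5% level) to detect 10% versus 15%; 80% power is reached for a difference of about 5.4 percentage points.* Use the same statement in the results paper. The cost is one sentence and a slightly less favourable power figure, with no extra participants and no change to the mailing schedule.

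Only if the sponsor prefers to keep 80% power for 5 points, change the stated size to about 690 per arm (1380 in total) and amend the 1200 in *Data processing and data collection* to match. At the planned 150 letters per week, mailing would then take 1380/150 = 9.2 weeks instead of 8, and the week-16 status query would have to move accordingly.

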### Data processing and data collection

Identification: Adults will be identified by NHS Digital only if they are registered with a consenting GP practice. Identification of eligible participants will take place using data contained within the Bowel Cancer Screening System which provides an up-to-date electronic record of uptake data for individuals enrolled in the national BSS.Data cleanse: NHS Digital will query the data of non-participants to identify type 2 opt-outs. Using the cleansed dataset, the first 1200 individuals will be selected to be included in the RCT database.Randomisation: NHS Digital will randomise eligible participants using the prerandomised dataset. The database will be split into two separate files with an equal number of people in each document using the study groups.Intervention: NHS Digital will share the data associated with each mail-out for the intervention and the control group with the mailing company called CFH Docmail Limited. CFH Docmail is an NHS Information Governance toolkit accredited mailing company that will be facilitating the mail merge throughout the study. The dataset will include study group, unique ID, personal contact details, NHS number and the practice name (only for intervention group). Reminders will be produced by merging each study group database with the reminder letter templates. The full package will include: the reminder letter, standard information booklet and a freepost return envelope. This process of sending previous non-participants a reminder 12 months after their initial invitation will continue until the study sample size (n=1200) is reached. We plan to send out 150 letters per week and send out all the reminders in 8 weeks.Data generation: once letters are sent, we will allow 8 weeks for all individuals to respond to the self-referral reminder. At the 16th week of the trial, NHS Digital will query the screening episode status of all individuals using their NHS numbers. If previous non-responders did not respond, their status will not change, and they will remain ‘non-responders’. If people confirmed and attended their appointment, they will be coded as ‘attended’. If people contacted the centre and cancelled their appointment and did not book another appointment, they will be considered ‘decliners’. If someone confirmed an appointment but did not attend, they will be coded as ‘non-attenders’. We will also request a separate category for those who have contacted the screening centre, had the initial confirmation and attended the clinic but not eligible to have the full investigation. People will be adequately screened, if they have had the full bowel scope investigation and received a definitive clinical result. For this purpose, we will additionally request the screening outcome of those who had the screening, and also information about the follow-up colonoscopy investigations. As a result, we will be able to distinguish between: (1) those who reacted to the self-referral reminders (responders) versus those who did not (non-responders), (2) those who successfully attended screening (attenders) versus those who did not (non-attenders) and (3) those who were adequately screened versus those who were not. In addition, NHS Digital will provide the Index of Multiple Deprivation (IMD) scores, using the postcodes of each individual included in the study.Data extraction: At the end of the study, after all data have been collated, the study database will be duplicated by NHS Digital. One copy will be anonymised for analysis by the University College London (UCL) research team. In the anonymisation process, all identifiable information including NHS number, full name, address, GP code and GP name will be excluded.Data deletion: Once the anonymised dataset is sent to the research team at UCL and verified, the research team will ask CFH Docmail to destroy all the datasets that were shared by NHS Digital. Only the research team at UCL will have access to the final dataset.
